## Abstract

**Background:**

Public safety personnel (PSP; e.g., border services personnel, correctional workers, firefighters, paramedics, police, public safety communicators) are frequently exposed to potentially psychologically traumatic events. Such events contribute to substantial and growing challenges from posttraumatic stress injuries (PTSIs), including but not limited to posttraumatic stress disorder.

**Methods:**

The current protocol paper describes the PSP PTSI Study (i.e., design, measures, materials, hypotheses, planned analyses, expected implications, and limitations), which was originally designed to evaluate an evidence-informed, proactive system of mental health assessment and training among Royal Canadian Mounted Police for delivery among diverse PSP (i.e., firefighters, municipal police, paramedics, public safety communicators). Specifically, the PSP PTSI Study will: (1) adapt, implement, and assess the impact of a system for ongoing (i.e., annual, monthly, daily) evidence-based assessments; (2) evaluate associations between demographic variables and PTSI; (3) longitudinally assess individual differences associated with PTSI; and, (4) assess the impact of providing diverse PSP with a tailored version of the Emotional Resilience Skills Training originally developed for the Royal Canadian Mounted Police in mitigating PTSIs based on the Unified Protocol for the Transdiagnostic Treatment of Emotional Disorders. Participants are assessed pre- and post-training, and then at a follow-up 1-year after training. The assessments include clinical interviews, self-report surveys including brief daily and monthly assessments, and daily biometric data. The current protocol paper also describes participant recruitment and developments to date.

**Discussion:**

The PSP PTSI Study is an opportunity to implement, test, and improve a set of evidence-based tools and training as part of an evidence-informed solution to protect PSP mental health. The current protocol paper provides details to inform and support translation of the PSP PTSI Study results as well as informing and supporting replication efforts by other researchers.

***Trial registration*:**

Hypotheses Registration: aspredicted.org, #90136. Registered 7 March 2022—Prospectively registered. Trial registration: ClinicalTrials.gov, NCT05530642. Registered 1 September 2022—Retrospectively registered. The subsequent PSP PTSI Study results are expected to benefit the mental health of all participants and, ultimately, all PSP.

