### Hypotheses

The PSP PTSI Study was registered with ClinicalTrials.gov (i.e., identification code NCT05530642), and the hypotheses were pre-registered.^1^ Hypotheses specific to individual difference variables are provided in Additional file 1: Tables (i.e., PTSI Measures; Primary Individual Differences Associated with Posttraumatic Stress Injuries; Secondary Individual Differences Associated with Posttraumatic Stress Injuries). Overarching PSP PTSI Study hypotheses:Participant mental health disorder prevalence rates at T1, based on Clinical Interviews or screening tools based on self-reported symptoms, will be higher than the general population [3, 97].From T1 to T2, participants will evidence reductions in risk, increases in resiliency, and improvements in mental health, as a function of the ERST [98, 99].Participants will evidence statistically significant predictive relationships between completing assessments and changes to individual differences over time (i.e., inversely with risk, positively with resilience, positively with mental health).Participants will evidence statistically significant sequential predictive relationships for environmental factors or individual differences reported during the *Daily Assessments*, *Monthly Assessments*, and *Full Assessments*.All participants will evidence sustained reductions in risk, increases in resilience, and increases in mental health at T3 relative to T2.Participants will evidence a statistically significant relationship between changes in individual differences over time and engagement with ERST content.Participants will evidence a statistically significant relationship between changes in environmental factors or individual differences over time, frequency of exercise [100], and other self-reported indicators of physical health [101].Relative to men, women will report more difficulties with mental disorder symptoms and occupational stressors.Diastole will be reduced in PSP who report symptoms consistent with one or more PTSI.The biometric data will be statistically significantly and substantively correlated with measures of PTSI.There will be a statistically significant and substantive relationship between PTSI symptom severity and reduced diastolic function.Changes in biological variables (i.e., autonomic nervous system reactivity, heart rate variability, cardiac mechanical changes) will be associated with environmental factors or individual differences.

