### Current study status and impacts of COVID-19

Recruitment began after a study launch meeting with the PSP sector leaders on September 22, 2020. COVID-19 substantially impacted the timelines for recruitment and training, as well as increasing the workload for all PSP, which reduced the individual capacity of participants to engage with novel training. In March 2021, a Steering Committee consisting of the PSP sector leads and the research team leads was established and recruitment began in earnest. Steering Committee meetings were held monthly for continued assistance with recruitment. Data collection began on October 20, 2021. T1 data collections for all participants were completed May 23, 2022. The T2 data collections for all participants are expected to conclude by August 19, 2022. The T3 data collections for all participants are expected to conclude by September 16, 2023.

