### Strengths and limitations

The PSP PTSI Study has several strengths including: (1) longitudinal design elements that can inform causal relationships; (2) prospective design elements that can inform predictive and proactive discussions associated with PPTE; (3) relatively large sample sizes; (4) ongoing multimodal assessments of environmental factors and individual differences, including PPTE exposures, occupational stressors, and social stressors; (5) inter-rater reliability assessments for clinical interviews; and, (6) being an ecologically valid test of the entire RCMP Protocol, including the ERST [56] across diverse PSP.

The PSP PTSI Study also has several necessary limitations. A truly randomized design was impossible because of how PSP interact within their professional environments. The already complex PSP environments were made more so by contemporary challenges with staffing and implementation requirements to protect public safety during the COVID-19 pandemic. Results from the RCMP Study will help address such limitations [56], as will having founded the ERST on the UP content that was based on randomized controlled studies [62, 63]. There is no obfuscation of the intended outcomes from ERST, which will create unknowable influence from expectancy effects. Direct research on such impacts remains nascent [117], but results suggest little or no difference between open and closed label designs when participants are provided with a sufficient study design rationale (e.g., [118]). The assessments are uncommonly detailed, which may produce intermittent participant response fatigue; however, participants were expressly informed about the rationale for the assessment details, which may help sustain morale. The detailed assessments also increase Type I error risks from spurious correlations [119]. The pre-registration of hypotheses, as well as the a priori provision of expected results in the current protocol paper are expected to mitigate Type I error risks and protect against equally problematic Type II error risks [119]. The voluntary nature of participation creates an unknowable influence from self-selection biases. The sample size, analytic plan, relatively short follow-up period, and provision of feedback through an electronic mental health record are designed to offset attrition.

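### The hypotheses registration is labelled prospective, but by the article's own dates it came 138 days into T1 data collection, which limits the Type I error protection claimed for it

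*Protocol article*

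**What the plan says.** The Trial registration paragraph of the abstract reports two registrations. The hypotheses, on aspredicted.org, are "Registered 7 March 2022—Prospectively registered". The ClinicalTrials.gov entry is "Registered 1 September 2022—Retrospectively registered". The Hypotheses section repeats that "the hypotheses were pre-registered".

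The section on current study status gives the calendar. For the start it states "Data collection began on October 20, 2021". It puts the close of T1 at 23 May 2022, the expected close of T2 at 19 August 2022 and that of T3 at 16 September 2023.

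Strengths and limitations concedes that the very detailed assessments raise the risk of Type I error through spurious correlations. It then answers: "The pre-registration of hypotheses, as well as the a priori provision of expected results in the current protocol paper are expected to mitigate" that risk. Separately, Planned analyses commits to controlling the familywise error rate, without naming a method.

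**The concern.** A registration is ordinarily called prospective when it precedes the data. This one did not, so the label and the calendar disagree.

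The label is also put to use. The article lists twelve overarching hypotheses and a very large set of measures, and it offers pre-registration as one of two mitigations of false positives. The other is the advance statement of expected results in the paper itself. That text already reports T1 as complete and cites a registration dated 1 September 2022, so it cannot be a priori for T1 data in the sense of preceding them.

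A reader who takes the label at face value would give confirmatory weight to results from data that already existed when the hypotheses were lodged. The most exposed is hypothesis 1 (counting in the order listed), which concerns disorder prevalence at T1. Hypotheses 8 to 11 (women versus men, diastole, biometric correlations, symptom severity and diastolic function) would be exposed in the same way if tested on T1 data alone.

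**Working it through.** The article states no interval between registration and data collection, so there is no figure to reproduce. The check is calendar arithmetic on its dates.

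**Inputs**
- Hypotheses registration: 7 March 2022 (abstract, Trial registration)
- ClinicalTrials.gov registration: 1 September 2022 (same place)
- Start of data collection: 20 October 2021 (current study status)
- End of T1: 23 May 2022 (current study status)
- Expected end of T2: 19 August 2022; expected end of T3: 16 September 2023 (current study status)
- T2 falls about 16 weeks after training commences (Data collection time frame)

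**Position of the registration within T1**
- Start of collection to registration: 11 (rest of October) + 30 + 31 + 31 + 28 + 7 = 138 days
- Registration to end of T1: 24 (rest of March) + 30 + 23 = 77 days
- T1 window: 138 + 77 = 215 days
- Share of the window elapsed: 138/215 = 64%. This is calendar time, not a share of participants or data, because the article gives no accrual by date.

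**Position relative to later milestones**
- Registration to expected end of T2: 165 days
- Registration to expected end of T3: 558 days
- Start of collection to ClinicalTrials.gov registration: 316 days

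**Could T2 data have preceded registration?**
- 16 weeks = 112 days. If training had begun on the first day of data collection, the earliest T2 would be 20 October 2021 + 112 days = 9 February 2022, which is 26 days before registration.
- Working backwards, 7 March 2022 − 112 days = 15 November 2021. Only participants whose training began by about that date could have reached T2 before registration.
- No training start date is given, and Recruitment and retention says schedules were arranged sector by sector. The question stays open.

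**Were the data accessible?**
- Data management and confidentiality says the study team had access while the study was running.
- The clinical interviews section has interviewers reading each participant's survey results before the interview.
- This establishes access, and sight of individual results. It does not establish that aggregate results were examined before 7 March 2022. The article makes no statement either way.

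**The case against.** The strongest reply is that what protects against data-driven hypotheses is registration before the data are inspected, not before they are collected. Nothing in the article shows that aggregate data were viewed before 7 March 2022. The footnote attached to the pre-registration statement and the aspredicted.org record are not in the text at hand, and either might state the position. The exposed hypotheses also have stated prior grounds: hypothesis 1 cites earlier work, the Gender and sex section reports earlier prevalence differences, and the biometrics section cites earlier findings on diastolic function. All of this stands. It makes post-hoc construction less plausible, but it does not make the label correct or supply the missing statement about data access.

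Several stronger readings are tempting, and the documents do not support them.

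- *That the hypotheses were shaped by the data.* The dates show opportunity only.
- *That pre-registration was the main or only Type I safeguard.* The limitations section names two mitigations and ranks neither, and familywise error control is planned separately.
- *That protection for the T1 to T2 change is also compromised.* This needs training to have started by about 15 November 2021, which is not stated. The text's citation of a 1 September 2022 registration does not settle it for T2 either, since the status section still speaks of T2 completion as expected.
- *That hypotheses 8 to 11 are T1-only.* They name no time point. Full assessments recur at T2 and T3, and cardiac recordings are taken daily.
- *That the two registrations are equivalent.* At the first, T1 was still open and the expected end of T2 was 165 days away. At the second, T1 had closed and the expected T2 end date had passed.

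**Conclusion.** The point holds as a mislabel with a limited inferential consequence. The hypotheses were registered 138 days after data collection began and 77 days before T1 closed, so calling the registration prospective, without qualification, is contradicted by the article itself. It did precede the expected end of T2 and, on the stated schedule, T3.

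The claim that pre-registration and a priori expected results mitigate Type I error is unsupported for data collected by 7 March 2022 unless those data were unseen. The claim for data collected after that date is not disturbed by this point. The conclusion rests only on the article's dates and on the usual meaning of prospective. It assumes nothing about what the team looked at. How many participants or observations are affected cannot be stated, because accrual by date is not given.

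**What to change.** 1. In the abstract, replace the prospective label with wording such as: *registered during T1 data collection, 138 days after it began, before the expected end of T2 and before T3*. Bring the Hypotheses section into line.
2. State which data had been extracted or examined by 7 March 2022. If none had been, one sentence saying so resolves most of the matter.
3. Unless none had been, report hypothesis 1, and any test of hypotheses 8 to 11 that is based only on T1 data, as not protected by prospective registration, that is, as exploratory.
4. Amend the Type I error sentence in Strengths and limitations to match. Note there that the expected results in the paper were finalised after T1 was complete, and that the familywise error control in Planned analyses still applies.

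There is no need to downgrade hypotheses 8 to 11 wholesale or to split the T1 to T2 contrast by calendar date. The documents do not call for either.

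The cost is a few sentences and a check of data access records. No measure, sample size or analysis model changes. The downside is that some T1 results may lose confirmatory status.

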**Supplementary Information:**

The online version contains supplementary material available at 10.1186/s40359-022-00989-0.

## Background

Public safety personnel (PSP; [1]) include diverse professionals (e.g., border services personnel, correctional workers, firefighters, operational and intelligence personnel, paramedics, police, public safety communicators, search and rescue personnel). PSP report extremely frequent and severe exposures to potentially psychologically traumatic events (PPTEs), often reporting more than 11 exposures to each different type of PPTE [2]. Nearly half (i.e., 44.5%) of PSP screen positive for one or more posttraumatic stress injuries (PTSI; e.g., major depressive disorder, panic disorder) at any given time [3]. Many PSP report suicidal behaviours during the past-year (i.e., ideation [10.1%], planning [4.1%], attempts [0.3%]) or during their lifetimes (i.e., ideation [27.8%], planning [13.3%], attempts [4.6%]) [4].

There are increasing commitments and efforts to provide evidence-based supports for PSP mental health [5, 6], but the available evidence regarding what will render the strongest effects remains sparse [7–11]. There are dozens of programs purported to support PSP mental health, most focusing on increasing knowledge, reducing stigma, and increasing help-seeking behaviors, but almost none have peer-reviewed research regarding effectiveness [7, 12]. Most of the peer-reviewed studies use cross-sectional data, short follow-up periods, and assess very small subsets of variables posited as important for mental health [7, 12, 13]. The limited available evidence suggests the extant programs produce benefits that are small, time-limited, and highly variable [8, 9, 11, 14, 15], due in part to low delivery fidelity [16] and insufficient mechanisms of action for mitigating PTSIs [7, 11, 12]. A particularly robust trial that compared psychoeducation to resilience training among PSP demonstrated no statistically significant differences between groups or over time in improvements on modifiable individual differences previously posited as PTSI risk factors [17].

Potentially modifiable risk factors for PTSI include elements of some personality traits (e.g., extraversion, conscientiousness, neuroticism, world view) [18, 19], hope [20], distress tolerance [21], optimism [22], interpersonal supports [23], and positive life activities (e.g., exercise) [24]. There are also individual differences on other psychological variables, such as anxiety sensitivity [25], fear of negative evaluation [26], illness/injury sensitivity [27], pain-related anxiety/fear [28], intolerance of uncertainty [29], rumination [30], maladaptive self-appraisal [31], dissociation [32], and anger [33], as well as differences in physiological variables, such as autonomic nervous system dysregulation [34–37]. Additional details regarding individual differences of interest for the PSP PTSI Study and the Royal Canadian Mounted Police (RCMP) Study are available in the Additional file 1. Environmental factors—such as PPTE and other stressors (e.g., adverse childhood experiences, difficult socioeconomic status) [38]—can also serve as risk factors for PTSIs. Other risk factors (e.g., family history of psychopathology [39] and aversive avoidant reactions to emotions) appear associated with PTSI development [25, 29] and may be managed by learning to accept and manage emotions instead of using avoidant coping strategies (e.g., alcohol and drug use, avoiding reminders of the event) [40–43].

The Unified Protocol for the Transdiagnostic Treatment of Emotional Disorders (UP) [41, 42] is an evidence-based cognitive-behavioral intervention designed to cultivate constructive approach-oriented emotional engagement. The UP is supported by considerable research evidence demonstrating transdiagnostic therapeutic effectiveness across several delivery formats (e.g., individual, group, self) [40, 44–48]. There is preliminary support from a randomized trial that the UP may be an effective proactive intervention to mitigate PTSI based on results from participants with elevated nonclinical symptoms of depression and anxiety reporting statistically significant improvements from baseline to 1-month follow-up [49]. The participants described the proactive UP training as highly satisfying and acceptable, and reported using the new skills “some” to “most” of the time, even at 1-month follow-up. The available evidence supports the UP as a promising proactive intervention that can be efficiently and effectively delivered to protect PSP mental health [13, 46, 50–54] and enhance job satisfaction [55].

In 2019, the RCMP undertook a large, multi-faceted, and multi-modal research study (i.e., “the RCMP Study”; www.rcmpstudy.ca) with several over-arching objectives [56]: (1) to develop, implement, and assess the impact of a system for ongoing (i.e., daily, monthly, annual) evidence-based biopsychosocial assessments (i.e., biometrics, clinical interviews, self-reported symptoms, social experiences); (2) to adapt the UP [40, 41], creating the Emotional Resilience Training (ERST); (3) to augment the RCMP Cadet Training Program [52, 57, 58] with the ERST to proactively mitigate PTSI; (4) to assess the impact of the tailored training on individual differences over time (i.e., pre-training, post-training, follow-up) and relative to the standard training; (5) to evaluate associations between demographic variables and PTSI symptoms; and, (6) to longitudinally assess individual differences associated with PTSI symptoms. The RCMP Study is a much-needed large-scale evaluation of a proactive, pervasive, and perpetual mental health assessment and training protocol designed to mitigate PTSI [12]. The RCMP Study required the development of several assessment protocols, as well as adapting the UP into the 13-week ERST and integrating the training into the RCMP Depot Division Cadet Training Program.

In 2020, the Canadian Institutes for Health Research awarded funding for “An Augmented Training Program for Preventing Post-Traumatic Stress Injuries Among Diverse Public Safety Personnel” (i.e., the PSP PTSI Study). The PSP PTSI Study was designed to adapt the RCMP Study protocols and ERST training [56] to accommodate a diverse range of participating PSP. The current protocol paper describes the PSP PTSI Study(i.e., design, measures, materials, hypotheses, planned analyses, expected implications, limitations), which is part of the concerted efforts being made by the Government of Canada, the Canadian Institutes for Health Research, and the Canadian Institute for Public Safety Research and Treatment to develop and implement evidence-based solutions to support PSP mental health [6].

The over-arching objectives for the PSP PTSI Study are to: (1) adapt, implement, and assess the impact of a system for ongoing (i.e., pre-training, post-training, follow-up, daily, monthly) evidence-based assessments of environmental factors and individual differences (i.e., measurements of biometrics, mental health, social experiences); (2) evaluate associations between demographic variables and symptoms of PTSI; (3) longitudinally assess environmental factors and individual differences associated with PTSI; (4) adapt the RCMP Study ERST to accommodate a diverse range of PSP; (5) implement the ERST with a diverse sample of PSP; (6) assess participant reactions to the ERST; and, (7) assess the impact of the ERST on individual differences and symptoms of PTSI over time. The current protocol paper: (1) details the PSP PTSI Study design, protocols, measures, materials, and hypotheses; and, (2) describes participant recruitment and study progress to date.

